5.1 Overall Trial Design

- A Phase IIa, open-label, randomized controlled trial with two arms:

1. Active treatment arm; Two dosing sessions with psilocybin 25mg with psychological support alongside TAU.

2. Active comparator control arm; TAU only.

TAU includes specialized care offered in an eating disorder unit in Region Skåne, Sweden. If the active treatment arm is determined to be safe, tolerable, and preliminarily effective during the follow-up assessment, participants in the control group will have the option to switch to the active treatment while maintaining their usual specialized care.

This design minimizes ethical concerns regarding withholding a potentially effective treatment.

Participants will be randomly assigned (1:1) to either the intervention or control group.

Block randomization stratified by age group (16–17 and 18–35 years) will ensure balanced representation.

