10.2 Statistical Analyses

This will be an open label, two-arm, active comparator (TAU; treatment as usual), , randomized controlled, between- and within-subjects, design in up to 40 completing patients meeting DSM-5 criteria for eating disorders. The patients will be randomly allocated to the psilocybin treatment-arm. The study analyses will enable comparison of efficacy between psilocybin-treatment and treatment as usual, as well as longitudinal within-patient efficacies.

- Primary Baseline Analyses:
  The primary analyses will involve descriptive statistics for demographic and baseline characteristics, ensuring comparability across groups, and control for follow-up measurements.
- Primary Endpoints analysis
- We will analyse differences in the number of participants and severity experiencing AE/SAE between the groups standardized forms for AE/SAE capturing: Event description, Start and end dates, Severity (e.g., mild, moderate, severe), Relatedness to intervention (assessed by safety review committee), Action taken.

The primary statistical methods will be:

- Descriptive Frequencies and Percentages.
- Comparing Proportions (Most Common for "Incidence") (Chi-squared test (or Fisher's Exact Test): Fisher's exact test is preferred for small cell counts (<5).
- Risk Ratio (RR) or Odds Ratio (OR) with Confidence Intervals: Report these measures of effect size to quantify the magnitude and precision of the difference between groups. An RR > 1 would indicate a higher risk in the intervention group.
- Comparing Severity and Relatedness is assessed with Mann-Whitney U test or Student t-test to compare severity distributions between groups.
- Secondary Endpoints:
  For secondary endpoints (e.g., changes in fMRI connectivity, BDNF, rating scales), group comparisons, including t-test, ANOVA, and Repeated Measures ANOVA will be utilized. When controlling for variables such as individual differences, ANCOVA or MANCOVA will be utilized. Principal component analysis (PCA) or independent component analysis (ICA) may be applied to identify patterns in fMRI data. Task-based fMRI data will be analysed using univariate models to investigate treatment effects in syndrome-related neural circuits (Celeghin et al., 2023; Bronleigh et al., 2022). Endpoints include longitudinal between- and within-person analyses.

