- When dichotomous (binary) outcome variables: Binary outcomes (e.g., remission, response rates) will be analyzed using logistic regression models, adjusting for baseline characteristics such as age, baseline BMI, and symptom severity. The odds ratios and 95% confidence intervals will be reported.
- When continuous (dimensional) variables (e.g., BMI, BDNF levels, cognitive flexibility) will be analyzed using linear mixed-effects models, and regression models of various types.
- Other: Exploratory Subgroup Analyses:
  Exploratory subgroup analyses will assess treatment effects across different strata (e.g., age groups, baseline severity) using interaction terms in regression models or stratified analyses to explore heterogeneity in treatment responses.
- Other: Sensitivity Analyses:
  Sensitivity analyses will address missing data using methods such as multiple imputation or maximum likelihood estimation. These methods ensure robustness of the findings by accounting for the potential impact of missing data on primary and secondary outcomes.

**Concomitant antidepressant treatment (yes/no; class; dose stability)** will be recorded and may be included as a covariate in exploratory analyses. Sensitivity analyses or subgroup analyses may be performed to explore potential moderating effects on clinical outcomes.

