10.3 Adjustment of Significance and Confidence Interval

A Bonferroni correction or false discovery rate (FDR) adjustment will be applied for multiple comparisons to control Type I error.

Results will be presented with 95% confidence intervals, and significance will be set at a two-tailed p-value of <0.05 after adjustments.

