10.4 Sample Size Calculations

No formal power calculation has been conducted due to the pilot nature of the study. However, 40 participants (20 per group) were chosen based on feasibility and alignment with recommendations for exploratory trials in emerging therapies​.

Post-hoc power analysis will assess the adequacy of the sample size in detecting clinically meaningful changes in primary outcomes.

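### Section 10.2 assigns the same continuous secondary endpoints to two unranked sets of methods and names neither the baseline value nor the randomisation age stratum as a covariate

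*Protocol*

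**What the plan says.** Section 10.2 of the Protocol gives the secondary-endpoint methods in two places.

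- The secondary-endpoints bullet opens with "For secondary endpoints (e.g., changes in fMRI connectivity, BDNF, rating scales" and goes on to say that "group comparisons, including t-test, ANOVA, and Repeated Measures ANOVA will be utilized". Its next sentence adds: "When controlling for variables such as individual differences, ANCOVA or MANCOVA will be utilized".
- A later bullet covers continuous variables in general, with BMI, BDNF levels and cognitive flexibility as examples. These "will be analyzed using linear mixed-effects models, and regression models of various types".

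Related text:

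- Named adjustment covariates (age, baseline BMI, symptom severity) appear only for the logistic models of binary outcomes.
- Multiple imputation or maximum likelihood is planned under sensitivity analyses.
- Section 10.1 defines the ITT population as everyone randomised.
- Section 5.1 stratifies the randomisation by age, 16–17 and 18–35.
- Section 4.4 sets the visits. Changes in AN symptom severity, well-being and personality run from baseline to the primary endpoint visit (Week 9), 6 months and 12 months. Changes in BDNF and fMRI run from baseline to Week 9 only.
- Section 7.4 lets control participants switch to psilocybin after the six-month follow-up, subject to the safety committee.

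**The concern.** Both bullets are commitments, and both cover the same endpoints: BDNF by name, rating scales and fMRI connectivity by scope. A t-test on change scores, an ANCOVA, a Repeated Measures ANOVA and a linear mixed model can give different estimates and standard errors from the same data, more so when visits are missing. With no main method named, the reported result depends on which sentence is followed. In an open-label trial that choice could be made after the data are seen.

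The listed methods also differ in efficiency. A plain t-test or ANOVA on change does not adjust for baseline as a covariate. Repeated Measures ANOVA in its standard form removes anyone with a gap. The mixed-model sentence names no baseline or stratum covariate either, so choosing it as written would not secure the adjustment. With 20 per arm, and limited power conceded in section 5.1, this is precision that could be had at no cost.

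**Working it through.** **Inputs from the Protocol.** "40 participants (20 per group) were chosen based on feasibility" (10.4). "Participants will be randomly assigned (1:1) to either the intervention or control group" (5.1). In 10.3, "significance will be set at a two-tailed p-value of <0.05 after adjustments"; the unadjusted 0.05 is used below, so the power figures are best case.

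**Inputs assumed.** There is no planned figure to reproduce: "No formal power calculation has been conducted due to the pilot nature of the study" (10.4). Assumed here are SD 1 at each visit, a true difference of 0.8 SD, rho from 0.3 to 0.7, and the missingness rates shown.

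**1. Complete cases under Repeated Measures ANOVA.** Section 4.4 gives three post-baseline visits for symptom severity. Take baseline as complete and missingness m as independent between visits. The number kept is 40 × (1 − m)³:

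- m = 3%: 40 × 0.913 = 36.5, about 37
- m = 5%: 40 × 0.857 = 34.3, about 34
- m = 10%: 40 × 0.729 = 29.2, about 29

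Independence is the harshest pattern. If the same people miss successive visits, more complete cases remain. For BDNF, with one post-baseline value in the endpoint definition, 5% missing leaves 40 × 0.95 = 38.

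**2. Precision from baseline adjustment.** Relative to the variance of a single follow-up value, the change score has variance 2(1 − rho) and ANCOVA has 1 − rho². The ratio is (1 − rho)(1 + rho) / [2(1 − rho)] = (1 + rho)/2. The number of patients a change-score t-test needs to match ANCOVA with 40 is 40 × 2/(1 + rho). Power and detectable differences come from the noncentral t distribution, 20 per arm, all complete.

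| rho | Variance ratio, ANCOVA/change | Power at 0.8 SD: change, ANCOVA | Detectable at 80% power (SD): change, ANCOVA | Patients for change score to match |
|---|---|---|---|---|
| 0.3 | 0.65 | 54.9%, 73.3% | 1.08, 0.87 | 61.5 |
| 0.5 | 0.75 | 69.3%, 81.2% | 0.91, 0.79 | 53.3 |
| 0.7 | 0.85 | 88.9%, 93.2% | 0.70, 0.65 | 47.1 |

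**3. Which part matters more.** A simulation used 1,500 runs, 40 patients, baseline plus three visits, rho 0.5 and 20% dropout depending on the previous value. It gave these standard errors for the final-visit arm difference:

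- complete-case change-score t-test: 0.360
- complete-case ANCOVA: 0.316
- likelihood model using all observed data: 0.309

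Baseline adjustment cuts the standard error by 1 − 0.316/0.360 = 12%. Using the partial records adds 1 − 0.309/0.316 = 2%. The likelihood model had known covariance and a common baseline mean, so 2% is favourable to it.

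**The case against.** The strongest reply is that 10.2 lists families of methods, as its examples suggest, and that choosing one model with its covariates and contrasts belongs in an SAP that is not shown. That would hold if the Protocol were silent. It instead commits to two different sets for the same endpoints, so an SAP that picks one as the main analysis must set the other aside.

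Several stronger readings are tempting, and the Protocol does not support them.

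- *The first set ignores baseline.* The endpoints are changes, so baseline is subtracted, and ANCOVA or MANCOVA is offered in the next sentence. What is missing is a commitment to use it and a named covariate. The opening bullet of 10.2 mentions control for follow-up measurements, but only alongside descriptive statistics and too loosely to fix one.
- *The whole first set discards incomplete cases.* Deletion across all visits belongs to Repeated Measures ANOVA. A t-test loses only those missing the values it uses. Imputation or likelihood methods are planned too, though only as sensitivity analyses.
- *The loss runs over all seven post-baseline EDE-Q visits in section 5.2* (40 × 0.97⁷, 0.95⁷ or 0.90⁷, about 32, 28 or 19 kept). Section 4.4 defines the symptom endpoint at three.
- *The result is biased because dropout differs by arm.* This is possible in an open-label trial, but nothing in the Protocol documents it.
- *Repeated Measures ANOVA breaks the ITT definition.* Section 10.1 says who is included, not how missing values are handled. The two fit poorly together, but this is not a strict contradiction.

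It also stands that these are secondary endpoints in a pilot whose primary endpoint is safety.

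**Conclusion.** The point holds as conflicting text plus a missing commitment to baseline and stratum adjustment for continuous outcomes. The conflict can be read directly from 10.2 and needs no assumption.

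The size rests on assumed inputs. For rho between 0.3 and 0.7, ANCOVA has 65% to 85% of the change-score variance, equivalent to about 47 to 62 patients instead of 40. The loss from dropping incomplete cases is secondary: about 3 to 11 of 40 participants under Repeated Measures ANOVA at 3% to 10% missingness per visit, with little precision regained by using their partial records. No bias has been shown. The change should be made, but neither the safety objective nor the validity of the trial depends on it.

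**What to change.** In section 10.2, name one main analysis for scalar continuous secondary endpoints, on all randomised participants:

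- Where the endpoint definition has several post-baseline visits, use a linear mixed model with arm, visit, arm-by-visit, baseline value and age stratum (16–17, 18–35), restricted to the visits in that definition. Three visits need 3 × 4/2 = 6 unstructured covariance parameters, against 7 × 8/2 = 28 if all seven EDE-Q visits were modelled.
- Where there is one post-baseline value, such as BDNF or an fMRI summary measure at Week 9, use ANCOVA with the same covariates.
- Remove t-test, ANOVA and Repeated Measures ANOVA for these endpoints, or label them descriptive. Drop the open reference to regression models of various types.
- Report the randomised arm difference with its 95% confidence interval at Week 9 and up to Month 6. Treat later arm comparisons separately and label them as such. After the switch in section 7.4, Month 12 may compare psilocybin with a control arm that has partly received it.

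The cost is wording only. The data are already collected, and the Protocol already names both types of model.

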4.2 Secondary Objectives

- To evaluate the efficacy of psilocybin with psychological support in reducing AN symptom compared to TAU and time to relapse within 12-month follow-up.

- To investigate potential mechanisms of action through neuroimaging (fMRI), using both resting-state and task-based paradigms for estimation, and biomarker analysis (BDNF levels) with in six-month follow-up.

- To assess changes in mental health, well-being, and personality traits within 12-month follow-up.

- To conduct a qualitative analysis of the subjective experiences of patients, their relatives, and therapists at last follow-up at 12 months.

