4.4 Secondary Endpoints

- Time to **Relapse:**

Defined as a composite outcome during the follow-up period, consisting of:

1. **≥7 % decrease in BMI** compared to post-hospitalization baseline BMI.

Rationale for 7 %: A 7% decrease in BMI reflects a significant deviation from expected weight gain in patients starting at a minimum BMI of 16, signaling potential relapse.

1. **Re-hospitalization for anorexia nervosa-related complications** (e.g., significant weight loss, medical instability). Data of hospitalization will be collected from hospital journal registers.
2. **Initiation of additional intensive psychiatric or nutritional interventions**, including day-patient or inpatient programs. Data of additional interventions will be collected from hospital journal registers.
3. **Self-reported significant deterioration in eating disorder symptoms** (e.g., severe food restriction, purging) as assessed by validated scales such as the Eating Disorder Examination Questionnaire 6.0 (EDE-Q 6.0).

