**Rationale for Composite Outcome:**
This composite endpoint captures both clinical (BMI, hospitalization) and patient-centered (symptom deterioration) measures, aligning with the study’s aim to evaluate the efficacy of psilocybin in reducing the risk of relapse during a critical recovery period.

- Time to **Response:**

A clinically significant improvement in weight and psychological symptoms during the treatment period.

**Criteria**: **BMI Increase**: ≥10% increase in BMI from baseline (e.g., BMI 16 → BMI 17.6) or reaching a BMI ≥18.5 if achievable within the study period.

- Time to **Remission:**

The achievement and maintenance of weight restoration and psychological well-being, with no significant symptoms of anorexia nervosa.

**Criteria**: **Weight Restoration**: BMI ≥18.5 sustained for at least four weeks, or a weight within 90-95% of ideal body weight adjusted for age and height.

- Changes in AN symptom severity (measured by the Eating Disorder Examination from baseline to primary endpoint and follow-up 6 and 12 months.

- Changes in well-being from baseline to primary endpoint and follow-up 6 and 12 month.

- Changes in personality traits from baseline to primary endpoint and follow-up 6 and 12 months

- Changes in brain resting state connectivity (measured by fMRI), and commonly used task-based fMRI paradigms from baseline to primary endpoint. The task-based paradigms will involve food-related conditions, commonly used in the population (Celeghin et al., 2023; Bronleigh et al., 2022) as well as established paradigms involved in processing reward anticipation (Knutson et al., 2000; Ventorp et al 2022)

- Changes in peripheral BDNF measured in platelet-poor EDTA plasma from baseline to primary endpoint.

5. Trial Design and Procedures

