**Intensive Follow-Up Phase Month 3,4 and 5**

Follow-up visits include:
- Eating Disorder Examination Questionnaire (EDE-Q)
- Columbia-Suicide Severity Rating Scale (C-SSRS)
- Brief Psychiatric Rating Scale – Extended (BPRS+)
- AE/SAE monitoring
- BMI, blood pressure, ECG
- Glucose, U-tox

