**Extended Follow-Up Phase**

9-Month Follow-Up

- Eating Disorder Examination Questionnaire (EDE-Q)
- Columbia-Suicide Severity Rating Scale (C-SSRS)
- Brief Psychiatric Rating Scale – Extended (BPRS+)
- AE/SAE monitoring
- BMI, blood pressure, ECG
- glucose, U-tox

12-Month Final Follow-Up
- Eating Disorder Examination Questionnaire (EDE-Q)
- Columbia-Suicide Severity Rating Scale (C-SSRS)
- Brief Psychiatric Rating Scale – Extended (BPRS+)

- Patient Health Questionnaire (PHQ-9)
- Generalized Anxiety Disorder scale (GAD-7)

- Ten Item Personality Inventory (TIPI)

- Meaningful Life Experience Rating (MLE).
- AE/SAE monitoring
- BMI, blood pressure, ECG
- glucose, U-tox

Participants who show signs of psychological or physical deterioration at any point during the study between follow-ups are instructed to contact the research team at any time and will be offered additional assessment and support.

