8.1 Methods for Measurement of Endpoints for Clinical Efficacy

Composite Relapse Endpoint:

- - BMI Decrease: Measured at baseline, 5 weeks, and 6 months using calibrated equipment and standardized protocols.
  - Hospitalization Data: Collected through patient reports and confirmed by medical records.
  - Symptom Deterioration: Assessed using validated tools such as the EDE-Q 6.0 and clinical interviews conducted by trained staff.
  - Clinical Intervention Use: Recorded in patient files, including initiation of new treatments during follow-up.

Changes in AN symptom (EDE-Q 6.0).

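### Relapse, response and remission are defined as times but no time-to-event method is named; sections 8.1 and 5.2 disagree on relapse BMI visits, and the 12-month visit lists no well-being scale

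*Protocol*

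**What the plan says.** **Endpoints.** Protocol section 4.4 lists time to relapse (a composite of BMI loss, re-hospitalisation, additional intensive intervention and self-reported deterioration), time to response and time to remission as secondary endpoints. Section 4.2 sets the horizon for the first: "time to relapse within 12-month follow-up".

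**Analysis.** Section 10.2 says: "Binary outcomes (e.g., remission, response rates) will be analyzed using logistic regression models", with odds ratios and 95% confidence intervals. For other secondary endpoints it names t-tests, ANOVA, repeated-measures ANOVA, ANCOVA or MANCOVA, linear mixed models and unspecified regression models. It names no survival method, and relapse is not assigned to any model by name.

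**BMI timing.** For the relapse composite, section 8.1 says BMI is "Measured at baseline, 5 weeks, and 6 months using calibrated equipment and standardized protocols". Section 5.2 lists BMI at baseline, at week 9, at months 3, 4 and 5 ("BMI, blood pressure, ECG"), at month 6, and again at months 9 and 12.

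**Well-being.** Section 4.4 includes: "Changes in well-being from baseline to primary endpoint and follow-up 6 and 12 month". In section 5.2 the entry headed "12-Month Final Follow-Up" lists EDE-Q, C-SSRS, BPRS+, PHQ-9, GAD-7, TIPI and MLE, but not SWLS, PANAS or HILS.

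**Switch.** Section 7.4 offers control participants psilocybin after the 6-month follow-up, once the safety committee is satisfied.

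**The concern.** An endpoint that is a time needs an analysis that uses the time. Logistic regression reduces response and remission to a yes or no at an unstated horizon. Someone who responds at week 9 counts the same as someone who responds at month 12, and the model has no place for a participant whose observation ends early. The possible switch of controls after month 6 adds to this, because a single 12-month yes or no cannot separate time before the switch from time after it.

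The two BMI schedules matter because BMI loss is the first component of relapse. Which section governs decides whether a BMI relapse can be dated to within a visit interval over the whole year, or only at two points in the first half.

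The well-being endpoint is a change score at month 12. If no well-being instrument is given at that visit, the score cannot be computed.

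**Working it through.** **1. The plan's own figures.** The response example in section 4.4 reproduces: 16 × 1.10 = 17.6. The relapse threshold for the same starting BMI is 16 × 0.93 = 14.88. The protocol states no event rate, dropout rate or effect size, and section 10.4 sets 40 participants on feasibility, so there is no power figure to reproduce.

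**2. Endpoint against method.**

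| Endpoint (4.4) | Model named in 10.2 | What it estimates |
|---|---|---|
| Time to response | Logistic | Odds of ever responding |
| Time to remission | Logistic | Odds of ever remitting |
| Time to relapse | None by name | Not stated |

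**3. Visit lists side by side.** Section 8.2 places the 6-month visit at week 24.

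| Visit | BMI in 8.1 | BMI in 5.2 | SWLS, PANAS, HILS in 5.2 |
|---|---|---|---|
| Baseline | yes | yes | yes |
| Day after each dosing | no | no | yes |
| Week 5 | yes | no | no |
| Week 9 | no | yes | yes |
| Months 3, 4, 5 | no | yes | no |
| Month 6 (week 24) | yes | yes | yes |
| Month 9 | no | yes | no |
| Month 12 | no | yes | no |

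Post-baseline BMI measurements number 2 under 8.1 and 1 + 3 + 1 + 1 + 1 = 7 under 5.2. The gap under 8.1 is 24 − 5 = 19 weeks, with nothing after month 6.

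MLE is in the 12-month list. However, section 5.2 groups it with the psychedelic-experience scales given the day after dosing, and it is not in the baseline list. No change from baseline can be formed from it.

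**4. What would be missed if 8.1 governed.** Assume a constant hazard and a 12-month relapse risk p. The risk by month 6 is 1 − (1 − p)^0.5, and the share of relapses after month 6 is (p − that risk) / p.

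- p = 0.30: risk by month 6 is 0.163; share after is (0.300 − 0.163)/0.300 = 0.456
- p = 0.50: risk by month 6 is 0.293; share after is (0.500 − 0.293)/0.500 = 0.414
- p = 0.60: risk by month 6 is 0.368; share after is (0.600 − 0.368)/0.600 = 0.387

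So about 39% to 46% of BMI relapses would fall after the last BMI, if BMI relapse follows this pattern. Relapse found through hospital registers or EDE-Q would still be seen.

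**5. Does a time-to-event method buy power?** Take 20 per arm, two-sided 0.05, an assumed control relapse of 50% and an assumed hazard ratio of 0.5.

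- Treated relapse: 1 − 0.5^0.5 = 0.293
- Expected events: 20 × 0.5 + 20 × 0.293 = 15.9
- Log-rank power (Schoenfeld): Φ(√(15.9/4) × 0.693 − 1.96) = Φ(−0.58) = 0.28
- Comparison of proportions, 0.50 against 0.293: 0.26

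Over control relapse of 30% to 60% and hazard ratios of 0.3 to 0.7, power is 8% to 69% for log-rank and 8% to 64% for proportions. The case for the change is that it fits the endpoint; power hardly moves.

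**The case against.** This is a pilot with safety as its primary endpoint. Section 5.1 admits limited between-group power, and a statistical analysis plan may supply methods. That stands for relapse: a missing model for it could be filled in later and would not be a finding alone. It does not cover response and remission, where the protocol names a method that does not estimate the endpoint it defines. Nor does it cover two sections that give different BMI visits for one component.

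Four stronger readings are tempting and do not hold.

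- *Relapse BMI stops at month 6.* That is only what section 8.1 says. Section 5.2 lists BMI at months 9 and 12. The defect is the contradiction.
- *The relapse endpoint cannot be estimated.* With the 5.2 visits, register-dated hospital events and EDE-Q through month 12, it can. Even under 8.1 only the BMI component would be lost after month 6.
- *There will be no 12-month well-being data.* The protocol does not say which scales define well-being, section 8.2 mentions unnamed other measures at 12 months, and the attached schedule is not shown. What can be said is that the three scales are absent from the 12-month list in section 5.2.
- *Unequal dropout will bias the odds ratio by a known amount.* Suppose no true effect, 50% relapse, leavers going at month 3 and counted as event-free, and dropout of 30% on TAU against 10% on psilocybin. Relapse by month 3 is 1 − 0.5^0.25 = 0.159. Observed risks are 0.7 × 0.5 + 0.3 × 0.159 = 0.398 and 0.9 × 0.5 + 0.1 × 0.159 = 0.466, an odds ratio of 1.32 (0.76 if the dropout rates are reversed). Every input is assumed, and relapse is not among the outcomes the logistic sentence names. Section 6.4 keeps those who stop dosing in follow-up, and section 10.2 has imputation or likelihood methods as sensitivity analyses. This shows a possible direction and does not measure bias in this trial.

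**Conclusion.** The point stands as three inconsistencies in the protocol's text. First, response and remission are times analysed as yes or no, with no time-to-event method named anywhere and no named model for relapse. Second, sections 8.1 and 5.2 give 2 and 7 post-baseline BMI measurements for the same component and disagree on week 5. If 8.1 governed, BMI relapse would be undated over 19 weeks and unseen after month 6. The 39% to 46% share after month 6 rests on a constant hazard and a 12-month risk of 30% to 60%, neither of which is in the protocol. Third, the 12-month change in well-being has no instrument with a baseline in the visit list of section 5.2, subject to the attached schedule.

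These are secondary endpoints in a small pilot, so the point should be corrected but does not threaten the primary safety objective.

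**What to change.** 1. **Analysis (section 10.2).** Use one time-to-event method for all three endpoints that suits detection at visits. One workable form is Kaplan-Meier curves with a log-rank test stratified by the randomisation age group (16–17, 18–35), on visit-dated events, with an interval-censored model as a sensitivity analysis. Keep logistic regression only as a supportive analysis at a stated time. Alternatively, redefine the endpoints as proportions at a fixed time and keep the logistic model.
2. **Switch.** State whether controls who switch after month 6 are censored at the switch, or limit the between-arm comparison to 6 months. Censoring at the switch or at dropout assumes that leaving is unrelated to prognosis; say so.
3. **BMI.** Reconcile section 8.1 with section 5.2 so that BMI from every 5.2 visit feeds the endpoint, and settle whether a week-5 BMI is taken.
4. **Well-being.** State which scales define it. Add those already used at month 6 to the 12-month visit, or drop month 12 from the endpoint.

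The cost is protocol wording and, at most, a few short questionnaires at an existing visit. Little or no power is gained.
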